1. A series of introductory school-based meetings will be led by [name] to describe the intervention study to parents and students, answer their questions, and invite them to participate. School administrators and the local school doctor will participate. (November/December 2008) Depending on availability, Drs. [name] will also participate.
2. At a second meeting, children and parents will complete an eligibility interview to assess disqualifying allergies to any intervention product. For eligible and willing participants, parents will complete an informed consent form and children will complete an informed assent form. (December 2008).
3. After consenting/assenting, children and their parents will complete a questionnaire, including questions regarding family socioeconomic status, a food frequency questionnaire, and ISAAC questions regarding wheezing/asthma and eczema.( Ellwood P, Asher MI, Beasley R, Clayton TO, Stewart AW. The International Study of Asthma and Allergies in Childhood (ISAAC): Phase Three rationale and methods. Int J Tuberc Lung Dis 2005; 9: 10-16.) This constitutes the first data collection of the study; thus we consider the data collection period to last from November through the end of the January-March intervention period. During the course of the study, the children will also complete a dairy checklist to assess dairy consumption in the first week of the trial, pre-vacation, post-vacation, and in the last week of the trial.

1. At baseline and at the conclusion of the study, professional phlebotomists (who will have completed human subjects training) will draw an 8ml sample into a red top tube. Blood draws will be done in the morning (8:00 to 10:00 am) to minimize for the diurnal variability in GH and other hormone levels. At the end of the intervention, samples will be taken on a Thursday or Friday, so that milk exposure during the school week will have its full effect, and any effect of weekend diet is minimized.

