4. 300 IU in 710 ml on schooldays of milk ‘substitute’ that has the same macronutrient and very nearly the same micronutrient content as cow’s milk. (n=150) The substitute is a vegetable-based macronutrient substitute for milk. It consists of: almond milk (Pacific); coconut milk (Taste of Thai); and wheat gluten (King Arthur). A non-nutritive thickener (Simply Thick) made from xantham gum is added to give the consistency of whole milk. The Pacific almond milk is fortified with calcium and vitamin D. The recipe is found in Appendix 11.
5. 300 IU vitamin D supplements on schooldays (n=100). (the first month will follow the following schedule to parallel the milk “phase-in: 100 IU/day for three days; 200 IU/day for two days; 300 IU/day thereafter)
6. Larger dose vitamin D supplements once a month (n=100). The maximum daily dose of the “monthly supplement” will be 2000 IU, per Institute of Medicine upper limits for children.[Standing Committee on the Scientific Evaluation of Dietary Reference Intakes FaNB, Institute of Medicine: Dietary Reference Intakes for Calcium, Phosphorus, Magnesium, Vitamin D, and Fluoride. National Academy Press, Washington, D.C., 1997. <http://books.nap.edu/openbook.php?record_id=5776&page=285> ] The “monthly dose” will in fact be spread over several days at the start of each month. (See table 1, in Section L.3C.7 above, for the detailed schedule.)

With the exception of the unfortified milk arm (arm #3), all arms will get 14,200 IU of vitamin D over the three months. Parents of children in the unfortified milk arm will receive an equivalent amount of vitamin D supplements at the conclusion of the trial.

We will use vitamin D tablets produced by Nature Made.

Randomization method for intervention and control groups:

We will use a mix of block and individual-level randomization. Some children will receive supplements (1 of 2 supplement regimens), while other children will receive milks (one of 4 milks). Since the milk is more desirable to children than supplements, it would be unacceptable to randomize children in the same classroom to milk or supplement. However, we think it is acceptable to have one classroom in a school be a supplement classroom, and the other a milk classroom. We do this to minimize socioeconomic confounding; our primary concern here is having equivalent baseline nutritional status across intervention arms.

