Ten schools will be selected using the criteria cited above. Each school will have two participating classrooms of roughly 40 children. We therefore need to randomize:

- ~200 children to one of two Supplement arms = 5 classrooms of ~40 children
- ~500 children to one of four Milk arms = 13 classrooms of ~40 children

Randomization procedure:

- Intervention schools will be randomly assigned to be one of the five ‘Mixed Intervention” or three “Milk Only Intervention” Schools by having [name] use a random-generator program to assign classrooms.
- Classrooms within the “Mixed Intervention” schools will be randomly assigned to supplement or milk intervention in a similar fashion by [name]. This will be done before the introductory school meetings, so that [name] can streamline the consent procedure to be specific to supplement or milk classrooms.
- Block randomization: within each S or M classroom, girls and boys will be chosen by gender-stratified random assignment to receive: monthly (n=20) or daily (n=20) supplements (in each S classroom); or US milk (n=12), fortified Mongolian milk (n=12), unfortified Mongolian milk (n=10), or almond milk (n=12) (in each M classrooms).

| School | 1 | | 2 | | 3 | | 4 | | 5 | | 6 | | 7 | | 8 | | 9 | | 10 | |
| --- | --- | --- | --- | --- | --- | --- | --- | --- | --- | --- | --- | --- | --- | --- | --- | --- | --- | --- | --- | --- |
| Classroom | S1 | M1 | S2 | M2 | S3 | M3 | S4 | M4 | S5 | M5 | M6 | M7 | M8 | M9 | M10 | M11 | M12 | M13 | M14 | M15 |
|  | 20:20 | 12:12:12:10 | etc |  |  |  |  |  |  |  |  |  |  |  |  |  |  |  |  |  |

Table 2.

Training:

- Drs. [name] and [name] will work with the HSPH HSC and Mongolian ERB to design a human subjects training session appropriate for the medical student volunteers (performing the anthropometric assessments, eczema examination, and CPT attention test), the local school doctors (who will report adverse events), and phlebotomists. Since many of our collaborators are not fluent in English, they cannot undergo the standard English-based human subjects research training (such as CITI). Per the suggestion of the HSPH HSC, we will instead design a training session for them in Mongolian. To that end, we have already translated the 4-page booklet on human subjects protection in research developed by the HSPH for international studies. This is attached in Appendix 3.
- Mongolian colleagues who are fluent in English will complete the online CITI training.

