##### Table 3: Adverse Event Grades

| Adverse Event | Grade | | | | |
| --- | --- | --- | --- | --- | --- |
|  | 0 | 1 | 2 | 3 | 4 |
| *Urticaria* *(hives, welts, wheals)* | None |  | Requiring no medication | Requiring PO or topical treatment | Requiring IV/IM medication |
| *Colitis* | None | Intermittent  abdominal pain, no change in daily functioning or diet | Abdominal pain with mucus and/or blood | Ileus or peritoneal signs |  |
| *Constipation* | None | Requiring stool softeners or dietary modification | Requiring laxatives | Obstipation |  |
| *Diarrhea* | None | Increase of <4 stools/day over pretreatment | Increase of 4-6 stools/day, or nocturnal stools | Increase of >7 stools per day or incontinence |  |
| *Dyspepsia/Heartburn* | None | Mild | Moderate | Severe |  |
| *Vomiting* | None | Mild nausea | 1 episode of vomiting in a 24 hour period | 2-5 episodes of vomiting in a 24-hour period. | Need for IV fluids |
| *Weight gain* | None | <5% | 5-<10% | 10-<20% |  |
| *Weight loss* | None | <5% | 5-<10% | 10-<20% |  |

1. Endpoints and comparisons

The primary endpoints include plasma vitamin D levels and somatotropin levels. The comparisons to be tested are numerically keyed to the table below.

The primary comparisons for the plasma vitamin D endpoints will be:

1. Post-pre intervention change in 25(OH)D for daily vs. monthly supplements (Aim 1a)

2. If there are no differences between supplement groups, then we will examine the change in

25(OH)D levels of the combined supplement groups versus the combined milk groups. If the

supplement levels are different, we will compare the change in the daily supplement group to

change in the combined fortified milk groups. (Aim 1b)

3. Change in 25(OH)D levels for combined fortified Mongolian milk group vs. unfortified

Mongolian milk (Aim 1c)

The primary comparisons for the somatotropin endpoints will be:

1. Post-intervention levels of GH and IGF-1 and IGF-1/IGFBP3 levels of Mongolian, U.S. fortified milks and the fortified milk substitute. (Aim 2b)

2. If there are no demonstrable differences in somatotropin levels between the two fortified

cow’s milks, we will combine the fortified cow’s milk groups to compare post-intervention

levels of GH, IGF-1, and IGF1/IGFBP3 levels for fortified cow’s milk vs. milk substitute.

(Aim 2a)

The secondary comparisons (eczema, asthma and respiratory infections) will be:

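### Fortification Study: families learn their classroom's milk or supplement assignment before consenting, so differential consent can bias contrasts between the two classroom types

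*Supplement*

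**What the plan says.** All references are to the Supplement, Fortification Study.

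- **Level of assignment.** Under the randomization method, milk versus supplement is set by classroom. The reason given is acceptability: "Since the milk is more desirable to children than supplements", "it would be unacceptable to randomize children in the same classroom to milk or supplement". Children are individually randomised only within a type: two regimens in supplement classrooms, four products in milk classrooms.
- **Timing.** Under the randomization procedure, the classroom assignment comes first: "This will be done before the introductory school meetings". The purpose is that staff "can streamline the consent procedure to be specific to supplement or milk classrooms".
- **Consent.** Under Intervention, families are invited at the introductory meetings and consent at a second meeting: "For eligible and willing participants, parents will complete an informed consent form".
- **Stated aim of the scheme.** "our primary concern here is having equivalent baseline nutritional status across intervention arms".
- **Contrast at stake.** Under Endpoints and comparisons, the second primary vitamin D comparison (Aim 1b) sets change in 25(OH)D "levels of the combined supplement groups versus the combined milk groups". If the two supplement groups differ, the daily group alone is compared with the fortified milks.
- **Later text.** Amendment #3 changes the number of schools and the calendar. No amendment changes the order of assignment and consent.

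**The concern.** For the milk-versus-supplement question the randomised unit is the classroom, and children are recruited after that unit's assignment is known and disclosed. Randomising classrooms makes the children eligible in each type comparable on average. It does not make the children who agree comparable if agreement depends on what is offered. The plan itself identifies a preference between the two offers.

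If some families join only when milk is offered, the consenting groups could differ in diet, poverty or baseline vitamin D. That is the imbalance the scheme was meant to avoid. Enrolling more children would not shrink the resulting bias.

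The acceptability argument does not cover this. It explains why milk and supplements are not mixed within a classroom. Assigning before consent is justified only by a simpler consent process, so the timing could change with classroom-level assignment left intact.

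**Working it through.** **1. Order of events.** Classroom assigned, then introductory meeting, then consent specific to the type, then baseline measures and intervention. Families know milk or supplement when they decide.

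**2. Contrasts affected.**

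| Contrast | Randomised at | Exposed? |
|---|---|---|
| Supplements vs milks (Aim 1b) | classroom | yes |
| Supplement vs unfortified milk (third hypothesis of Aim 1) | classroom | yes |
| Later models 1-2: daily and seasonal terms | classroom | yes |
| Later model 3: seasonal term, and the pooled any-daily term | classroom, wholly or in part | yes |
| Later models 4-5: milk terms against daily supplement | classroom | yes |
| Daily vs monthly supplement | child, within classroom | no |
| Fortified vs unfortified Mongolian milk (including growth paper) | child, within classroom | no |
| Milk vs milk substitute | child, within classroom | no |

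**3. The plan's benchmark.** Table 5 gives 0.30 SD, or 3.7 to 7.5 nmol/L, for any supplement versus Mongolian fortified milk at 200:150. With two-sided alpha 0.05 (sidedness is not stated) and 80% power:

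(1.960 + 0.842) × √(1/200 + 1/150) = 2.802 × 0.1080 = 0.303 SD.

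Power at 0.30 SD is 79.3%, so the figure reproduces. At the assumed SDs of 12.5 and 25 nmol/L, 0.30 SD is 3.75 and 7.5 nmol/L. The calculation assumes exchangeable arms and makes no allowance for recruitment bias. The plan's minimum clinically meaningful difference is 12 nmol/L.

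**4. Illustrative bias.** The documents give no consent rates, so these inputs are assumptions:
- consent in milk classrooms, p_m = 0.90 to 0.95
- consent in supplement classrooms, p_s = 0.60 to 0.80
- everyone who would accept supplements would also accept milk
- children who join only for milk differ in 25(OH)D change by δ = 5 to 10 nmol/L, in either direction.

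The share of milk consenters who would have declined supplements is f = (p_m − p_s)/p_m, and the bias is f × δ.

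| p_m | p_s | f | Bias, δ = 5 | Bias, δ = 10 |
|---|---|---|---|---|
| 0.90 | 0.80 | 0.111 | 0.56 | 1.11 |
| 0.95 | 0.75 | 0.211 | 1.05 | 2.11 |
| 0.95 | 0.60 | 0.368 | 1.84 | 3.68 |

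The range is about 0.6 to 3.7 nmol/L. If selection is equal in both types, the bias is zero.

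**5. Cross-check by a second model.** Suppose consent depends on a latent willingness correlated 0.1-0.5 with the outcome, with 95% consent for milk and 70-80% for supplements (again assumed). The shift is then 0.02-0.19 SD, or 0.3-4.9 nmol/L over SDs of 12.5-25. The order of magnitude is the same.

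**6. Effect on the test.** With no true effect, independent children and a shift of b SD, the rejection probability is Φ(b/SE − 1.96) + Φ(−b/SE − 1.96), where SE = √(1/n₁ + 1/n₂).

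| Sizes | b = 0.05 | b = 0.10 | b = 0.20 |
|---|---|---|---|
| 200:150 | 7.5% | 15.2% | 45.7% |
| 200:300 | 8.5% | 19.5% | 59.1% |
| 100:300 | 7.2% | 13.9% | 41.0% |

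The last two rows are pooled supplements, and daily supplement alone, against the two fortified cow's milks.

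**7. Existing safeguards.**
- Change scores remove fixed differences in level but not differences in response. The plan allows that response may depend on baseline: later model 6 includes an interaction between arm and low baseline 25(OH)D.
- The covariate check includes socioeconomic status and baseline vitamin D, but it sees only children who consented and prescribes no action.
- School as a fixed effect does not remove a consent difference between classrooms in the same school, and a random classroom effect does not correct a systematic shift between types.
- Later models 1-5 adjust for school, gender, age and, in one version, completion. They omit baseline 25(OH)D and socioeconomic status.

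**The case against.** **Size.** Every input to the bias is assumed. The assumed 5-10 nmol/L difference is 0.4-0.8 SD at the lower SD (5/12.5, 10/12.5) and 0.2-0.4 SD at the higher. The 3.7 figure needs the widest consent gap and the largest difference together. The whole range lies below a third of the 12 nmol/L meaningful difference. This stands, and the figures are illustrations only. It does not dispose of the point, because the plan expects small differences between arms that deliver equal vitamin D and wants intervals tight enough to establish equivalence. A few nmol/L matter for that purpose.

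**Preference.** The plan says children prefer milk. It does not say parents would refuse supplements, and parents give consent. It even promises supplements afterwards to the unfortified-milk children. A reader might infer that consent did differ, or that the milk and supplement groups are known to be unequal. The documents support neither; they show only that the order permits it.

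**Scope.** A reader might also infer that the vitamin D and growth results are compromised. They are not on this ground, because fortified versus unfortified Mongolian milk is randomised within classrooms.

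**Consent forms.** The appendix list names one consent form and one assent form, and the forms are not available here. How far the final wording differed by classroom type cannot be checked. The stated intention, however, is plain.

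**Remedy.** If many families would decline supplements, they could leave once the assignment is revealed. They would have no follow-up 25(OH)D and would drop out of a complete-case change analysis. This largely stands: later disclosure reduces and exposes the selection but cannot abolish it.

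**Conclusion.** The point holds as a design weakness limited to contrasts between classroom types. Recruitment follows a known assignment, one offer is acknowledged to be more attractive to children, and the only reason given for the order is convenience.

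The direction is unknown and the size cannot be derived from the documents. Under the stated assumptions the bias is about 0.6-3.7 nmol/L, and zero if selection is equal. That is short of the plan's clinically meaningful difference. At the top of the range it roughly equals the smallest detectable difference for pooled supplements versus Mongolian fortified milk if the SD is 12.5 nmol/L, and about half of it if the SD is 25 (3.7 against 7.5). Existing safeguards are real but partial. The change is worth making because it is cheap and protects a primary comparison.

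**What to change.** - Keep classroom-level assignment. Use one meeting script and one consent/assent form describing both possibilities, complete consent and baseline blood and measurements, and only then reveal the classroom's assignment. A form covering several products is feasible, since milk classrooms already require one for four.
- Report eligible, invited and consenting children, and those withdrawing after the reveal, by classroom and classroom type.
- Add baseline 25(OH)D and household socioeconomic status to the prespecified milk-versus-supplement models.
- State that Aim 1b and the related models rest on classroom-level assignment, unlike the within-classroom contrasts.

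**Cost.** The form and meeting are somewhat longer. Some children give an 8 ml baseline sample before knowing what they will receive. Families who leave after the reveal will lack follow-up 25(OH)D, though they are then visible as withdrawals with baseline data. If recruitment is already complete, the reporting and adjustment can still be done as far as records allow.

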##### Table 3: Adverse Event Grades

| Adverse Event | Grade | | | | |
| --- | --- | --- | --- | --- | --- |
|  | 0 | 1 | 2 | 3 | 4 |
| *Urticaria* *(hives, welts, wheals)* | None |  | Requiring no medication | Requiring PO or topical treatment | Requiring IV/IM medication |
| *Colitis* | None | Intermittent  abdominal pain, no change in daily functioning or diet | Abdominal pain with mucus and/or blood | Ileus or peritoneal signs |  |
| *Constipation* | None | Requiring stool softeners or dietary modification | Requiring laxatives | Obstipation |  |
| *Diarrhea* | None | Increase of <4 stools/day over pretreatment | Increase of 4-6 stools/day, or nocturnal stools | Increase of >7 stools per day or incontinence |  |
| *Dyspepsia/Heartburn* | None | Mild | Moderate | Severe |  |
| *Vomiting* | None | Mild nausea | 1 episode of vomiting in a 24 hour period | 2-5 episodes of vomiting in a 24-hour period. | Need for IV fluids |
| *Weight gain* | None | <5% | 5-<10% | 10-<20% |  |
| *Weight loss* | None | <5% | 5-<10% | 10-<20% |  |

1. Endpoints and comparisons

The primary endpoints include plasma vitamin D levels and somatotropin levels. The comparisons to be tested are numerically keyed to the table below.

The primary comparisons for the plasma vitamin D endpoints will be:

1. Post-pre intervention change in 25(OH)D for daily vs. monthly supplements (Aim 1a)

2. If there are no differences between supplement groups, then we will examine the change in

25(OH)D levels of the combined supplement groups versus the combined milk groups. If the

supplement levels are different, we will compare the change in the daily supplement group to

change in the combined fortified milk groups. (Aim 1b)

3. Change in 25(OH)D levels for combined fortified Mongolian milk group vs. unfortified

Mongolian milk (Aim 1c)

The primary comparisons for the somatotropin endpoints will be:

1. Post-intervention levels of GH and IGF-1 and IGF-1/IGFBP3 levels of Mongolian, U.S. fortified milks and the fortified milk substitute. (Aim 2b)

2. If there are no demonstrable differences in somatotropin levels between the two fortified

cow’s milks, we will combine the fortified cow’s milk groups to compare post-intervention

levels of GH, IGF-1, and IGF1/IGFBP3 levels for fortified cow’s milk vs. milk substitute.

(Aim 2a)

The secondary comparisons (eczema, asthma and respiratory infections) will be:

To determine sample sizes, we first debated the smallest clinically interesting contrast in vitamin D between arms. Since all arms (except the n=100 unfortified Mongolian milk arm) deliver the equivalent amount of vitamin D3, we anticipate small differences between them. We felt it would be as useful to definitively establish equivalency between arms as it would be to detect clinically meaningful differences; for that reason, we propose a well-powered study that can deliver tight confidence intervals. We felt that the minimum clinically meaningful difference would be 12 nmol/L (5 ng/ml). Accordingly, we designed a study to detect differences <12 nmol/L with 80% power.

In Table 5 below, we show the minimum standard deviation difference in mean 25(OH)D levels between the post-intervention arms, setting Type 1 error (alpha) to 0.05 and Type 2 error (beta) to 0.80. We used PASS statistical software for our calculations. These power calculations are conservative, in that they don’t take advantage of the pre-intervention data, which can be used to measure within-individual change. In our pilot study, we observed mean + standard deviation (s.d.) 25(OH)D levels of 43.1 + 12.0 nmol/L (17.3 + 4.8 ng/ml) at the outset of the intervention and 66.1 + 11.2 nmol/L (26.5 + 4.5 ng/ml) at the end of the one month intervention in Ulaanbaatar from May to June. These are consistent with data from adolescents in Boston winter (20.2 + 9.9 ng/ml) (Arch Pediatr Adolesc Med. 2004;158:531-537) and children in northern Spain in March (12.6 + 5.5 ng/ml).(**J Bone and Mineral Research 1998;13:544-548)** To translate the minimum detectable s.d. into clinically meaningful units of 25(OH)D, we assumed s.d.’s of 12.5 and 25 nmol/L (5 and 10 ng/ml).

Table 5.

| Contrast | N | Minimum Detectable SD units | Translation of SD into 25(OH)D units: smallest difference we could distinguish from zero with 80% power* |
| --- | --- | --- | --- |
| Monthly v. daily supplement | 100:100 | 0.40 | 5.0 to 10 nmol/L  (2.0 to 4.0 ng/ml) |
| Either supplement vs. Mongolian fortified milk; Mongolian unfortified vs. fortified milk | 100:150 | 0.36 | 4.5 to 9 nmol/L  (1.8 to 3.6 ng/ml) |
| Any supplement vs. Mongolian fortified milk | 200:150 | 0.30 | 3.7 to 7.5 nmol/L  (1.5 to 3.0 n/ml) |
| Contrast between any two fortified milks | 150:150 | 0.32 | 4.0 to 8.0 nmol/L  (1.6 to 3.2 ng/ml) |

*Assumes s.d. of 5-10 ng/mL for 25(OHD) comparisons

For the aim of examining IGF-1 and GH differences between fortified milk arms, the sample size for the primary comparisons is 150:150 (any given cow’s milk compared with milk substitute, or a contrast between two cow’s milks). As the clinical significance of changes in IGF-1 and GH within the normal range are unknown, we simply powered the study to detect changes on the order of those observed in our pilot studies. In Boston (one week intervention with macronutrient control) we observed 0.2 sd higher levels of IGF-1 and 0.4 sd higher levels of GH during the “milk week”; in Mongolia (one month intervention without macronutrient control), we observed 0.7 s.d. higher levels of IGF-1 and 0.3 s.d. higher levels of GH after the month-long milk intervention. The 150:150 contrast yields 80% power to detect differences as small as 0.3 s.d.’s, which is in the range of the contrasts we observed in the pilot studies.

1. Data storage and data security

At enrollment, the participants will be issued study ID numbers, which will be used to identify their data forms and blood samples thereafter. We will maintain the link between student identifiers and study ID in a locked file in [name] office and in a password-protected electronic file accessible only to [name], [name], and designated (trained) assistants. It is necessary to maintain this linkage so that we can give the vitamin D results to the families after the samples are analyzed at the end of the study. After that point, the linkage will be destroyed.

The linkage between the participant identifiers and study ID will be destroyed on December 31, 2009, after the samples are analyzed and vitamin D results communicated to the families. We will hold on to the de-identified data for two more years to fully analyze it.

Study findings will be shared with the school community and the subjects after the study has been completed. We will return with results in the summer or fall of 2009. At a minimum, we will meet with Ministry officials and parents to communicate the study results. If we can find additional funds, we hope to hold a national conference to share the results more broadly.

At the end of the study, we plan to give the pre-intervention and post-intervention vitamin D levels to the families. [name] will present the overall study results at a school meeting, and each parent will receive an envelope with their child’s vitamin D levels and an indication of whether the levels were above or below normal (50 nmol/L or 20 ng/ml). [name] and the school doctor will be on hand to answer questions and make suggestions about how low levels of vitamin D deficiency can be treated and prevented with resources available in Mongolia. There are no interim results, since pre-intervention and post-intervention samples will be analyzed together at the end of the study.

LIST OF APPENDICES INCLUDED IN THE ORIGINAL APPLICATION:

1. Letter to parents describing the study
2. Script for the evening meeting with parents and children explaining the study
3. HSPH HSC Human subjects pamphlet: Mongolian version
4. Baseline questionnaire
5. Dairy Checklist
6. Classroom Behavior Questionnaire
